## Methods

### Trial Design

A parallel, evaluator-blind RCT conducted at two sites (Vancouver, British Columbia and London, Ontario) will be used. To minimize participants’ bias associated with knowing which intervention is of interest to researchers, we will attempt to mask participants to the true study objectives (NCT01942798). This will be achieved thorough stating that “evidence suggests that having good cognition improves physical outcomes and we are trying to determine whether cognitive or activity training is better” both in the consent form and when addressing subjects’ comments/questions.

Participants will be stratified by site and block randomized to the Wii.n.Walk intervention or control group in triplets using a 1:1 allocation ratio. To ensure balance between groups and masking of group assignment, a central computerized randomization process will be designed by the research team statistician, with undisclosed variable block sizes. Randomization will occur after the participant is screened and enrolled (Figure 1). The site coordinators will contact the statistician via telephone or email and obtain group assignment. The participant’s contact information will be forwarded to the appropriate group trainer to arrange for an initial training session.

This trial includes a supervised and an unsupervised phase for both the Wii.n.Walk intervention and control group. Once enrollment has been completed, participants will be evaluated on a number of clinical measures at baseline, after the supervised phase is completed, after the unsupervised phase is completed, and at a 1-year follow-up time point.

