### Primary Analysis

To account for any within-cluster correlation that may occur as a result of delivering the intervention in groups, ICC will be calculated among the outcomes of participants within the same groups (clusters). Variation inflation factor (VIF) will be calculated using the formula: VIF=1+ICC(M−1) [76-78]. The M variable refers to the cluster size, which equals 3 in this study. Post-treatment walking capacity scores will be compared in the Wii.n.Walk and control groups using analysis of covariance (ANCOVA) for the end of supervised phase, end of unsupervised phase, and end of retention period, controlling for site, baseline score, and possibly amputation level and age [79]. To adjust for clustering effect, the ANCOVA’s *F* statistics will be divided by the VIF [76,77]. Missing data will be handled using Multiple Imputation [80]. A sensitivity analysis will also be conducted to evaluate the impact of missing data [81]. Significance testing (*P*) and marginal means with 95% confidence intervals will be estimated. Effect size (partial eta squared) will be calculated as a ratio of the effect and total sums of squares, with a 95% confidence interval. Primary analysis will be based on intention-to-treat to include all randomized participants. However, secondary analysis on a per-protocol basis (participants who adhere to treatment) will also be conducted for comparison [82].

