### Sample Size Calculation

The primary outcome (2MWT) was used to calculate the sample size. The responsiveness of the 2MWT in a single study that included older adults with LLA being discharged from rehabilitation had a mean of 13.6 (SD 19.9) meters [52]. In an RCT of younger (mean age 36 years) community-dwelling individuals with LLA, the mean difference between treatment and control groups was 11.2 (SD 18.4) meters [43]. Walking distance gains from our own pilot work (mean 25, SD 18.1 meters) on younger adults in rehabilitation [30], and early results from our feasibility study (mean 11.9, SD 9.3 meters) using a similar sample as the proposed study, suggests distances of up to 14 meter gains may be possible. Taking into account these data and based on our study team’s considerable clinical expertise, we decided that the minimal clinically important difference of 14 meters would be reasonable. Using the sample size calculation formula for ANCOVA in RCTs (α=.05; β=.1; rho=.72) [82], each group would require 21 participants. Borm et al [83] demonstrate that when rho lies between .2 and .8, ANCOVA further reduces the required sample size by 10-40% over change score. Accounting for an additional 4 degrees of freedom (one stratification factor for site at randomization and possibly three at analysis), an extra four participants per group (n=25) are required. Accounting for a conservative total group dropout rate of 25% and supported by physical activity clinical trials (8-24%) [84,85], 64 participants are required. Because the supervised sessions are conducted in groups of three, the sample size needs to be divisible by three. Therefore, a final n=72 will allow us to enroll a balanced n of 18 Wii.n.Walk and 18 controls at each site.

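### The effect size is labelled partial eta squared but defined by the formula for ordinary eta squared; in this ANCOVA the two give different values

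*Protocol article*

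**What the plan says.** The Primary Analysis section of the protocol article compares post-treatment 2MWT scores between arms by ANCOVA, "controlling for site, baseline score, and possibly amputation level and age". The F statistic is divided by a variance inflation factor (VIF) because training is delivered in groups of three. The section promises P values and marginal means with 95% confidence intervals. For the effect size it then says: "Effect size (partial eta squared) will be calculated as a ratio of the effect and total sums of squares", also with a 95% confidence interval.

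The Sample Size Calculation section gives the planning values "α=.05; β=.1; rho=.72" and a "minimal clinically important difference of 14 meters would be reasonable", and arrives at 21 per group before allowances. No other section defines or qualifies the effect size.

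**The concern.** The sentence names one statistic and gives the formula of another. Partial eta squared is SS_effect / (SS_effect + SS_error). Effect over total is ordinary eta squared. The two coincide only when no other term in the model explains any variance. Here baseline walking distance is in the model and is expected to be strongly prognostic. Partial eta squared leaves the variation explained by baseline out of its denominator; the written formula keeps it in.

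Two analysts working from this sentence could therefore report clearly different numbers from the same data. A reader who sees the label partial eta squared on a value computed from the total sum of squares would take the covariate-adjusted effect to be smaller than it was.

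**Working it through.** **Inputs**

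- Target difference: 14 m (Sample Size Calculation).
- Alpha .05, power .90, correlation between baseline and follow-up .72 (same section). Sidedness is not stated; two-sided is assumed.
- Allocation 1:1 (Trial Design).
- SD: not stated for the calculation. The section lists 19.9, 18.4, 18.1 and 9.3 m from different sources.

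**Step 1: reproduce the plan's 21 per group.** n = 2 × [SD × (z for two-sided .05 + z for 90% power) / 14]² × (1 − rho²).

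- SD 19.9: 42.46 × (1 − .5184) = 20.45, rounded up to **21**, as stated.
- SD 18.4 gives 18, SD 18.1 gives 17 and SD 9.3 gives 5.
- One-sided with SD 19.9 gives 17.

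Of the quoted SDs, only 19.9 m, used as the outcome SD with a two-sided test, gives 21. It is used below as an inferred input.

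**Step 2: the two measures at those inputs.** Per participant, with equal arms:

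- Effect: (14/2)² = 49.
- Within-arm variance: 19.9² = 396.0.
- Error after baseline: 396.0 × (1 − .5184) = 190.7.
- Total: 396.0 + 49 = 445.0.
- Partial eta squared: 49 / (49 + 190.7) = 49 / 239.7 = **.204**.
- Formula as written: 49 / 445.0 = **.110**.
- Ratio: 239.7 / 445.0 = .539, so the written formula is 46% lower.

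The gap equals the share of the total sum of squares taken by baseline: 396.0 × .5184 = 205.3, and 205.3 / 445.0 = 46%. This differs from rho² = 52%, which is baseline's share of the within-arm variance only.

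**Step 3: check by simulation.** Simulated ANCOVAs with baseline and site as covariates, independent outcomes and 4,000 runs per sample size gave mean values of .120 against .223 at 25 per arm and .116 against .217 at 36 per arm. The ratio was about .54 in both cases.

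**Step 4: how far the size depends on the inputs.**

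| Varied input | Formula as written | Partial | Written value lower by |
|---|---|---|---|
| 14 m, rho .72, SD 18.4 | .126 | .231 | 45% |
| 14 m, rho .72, SD 18.1 | .130 | .237 | 45% |
| 14 m, rho .72, SD 9.3 | .362 | .541 | 33% |
| 14 m, rho .72, SD 26.6 | .065 | .126 | 48% |
| 14 m, SD 19.9, rho .2 | .110 | .114 | 4% |
| 14 m, SD 19.9, rho .5 | .110 | .142 | 22% |
| 14 m, SD 19.9, rho .8 | .110 | .256 | 57% |
| 11.2 m, SD 19.9, rho .72 | .073 | .141 | 48% |

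The SD of 26.6 m applies if 19.9 m is an SD of change, as its source suggests ("had a mean of 13.6 (SD 19.9) meters", given as responsiveness). The post-score SD is then 19.9 / √(2 × (1 − .72)) = 26.6, assuming equal SDs at both times.

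**The case against.** The strongest reply is that this is a slip in a descriptive clause. If the analysts follow the label, for instance by taking partial eta squared from their software, the reported value is correct and only the stated formula is wrong. That stands: the article does not say whether label or formula governs, so a reader who infers that the trial will publish an effect size 46% too low goes further than the text allows. What it supports is an inconsistency, with a wrong value under its label if the formula is followed.

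A reader might also infer that the primary inference is compromised. It is not: the F test, its VIF adjustment, the P value, the marginal means and the sample size do not use this ratio. Nor is it shown that evidence syntheses would be misled, since marginal means with 95% confidence intervals are already promised and carry the effect in meters.

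The size is conditional too. The SD of 19.9 m is inferred, and the absolute values change markedly if it is an SD of change. The feasibility study, described as using a similar sample, has an SD of 9.3 m, which gives 33%.

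Two other replies do not stand. Reading total as effect plus error conflicts with the usual meaning of the total sum of squares in ANCOVA, which includes what the covariates explain. Leaving the matter to a fuller analysis plan does not help either, because the article does not omit the formula; it states one that does not match its label.

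**Conclusion.** The label and the formula name different statistics, and this holds whatever the numbers. With baseline and site in the model they give different values. If the formula is followed, the figure reported as partial eta squared would be about 46% too low (.110 against .204). This assumes a 14 m difference, rho=.72, 1:1 allocation and the inferred SD of 19.9 m. The range is 33% to 48% across the other SDs considered at rho=.72, and 4% to 57% for rho from .2 to .8 at SD 19.9 m. Prognostic value in amputation level or age, should they be added, would widen the gap. The consequence is confined to the reported effect size and its 95% confidence interval.

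**What to change.** Choose one of two wordings in the Primary Analysis section:

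- keep the label and define partial eta squared as SS_effect / (SS_effect + SS_error); or
- if the total sum of squares is intended, keep the formula and call the measure eta squared.

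Either is acceptable. In both cases, derive the 95% confidence interval for the quantity actually named and say how it respects the clustering adjustment. For a one-degree-of-freedom effect, partial eta squared equals F / (F + error degrees of freedom), so an interval built from the undivided F would ignore the clustering that the VIF-divided F is meant to allow for.

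The cost is one corrected formula or label and a sentence on the interval. Design, data collection and the primary test do not change.

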### Secondary/ Tertiary Analyses

ANCOVA with an adjusted *F* statistic (as explained above) will be used to compare post-treatment scores between groups for secondary and tertiary outcomes. Confidence intervals (95%) will be derived. Mean percent adherence will be calculated.

### Sample Size Calculation

The primary outcome (2MWT) was used to calculate the sample size. The responsiveness of the 2MWT in a single study that included older adults with LLA being discharged from rehabilitation had a mean of 13.6 (SD 19.9) meters [52]. In an RCT of younger (mean age 36 years) community-dwelling individuals with LLA, the mean difference between treatment and control groups was 11.2 (SD 18.4) meters [43]. Walking distance gains from our own pilot work (mean 25, SD 18.1 meters) on younger adults in rehabilitation [30], and early results from our feasibility study (mean 11.9, SD 9.3 meters) using a similar sample as the proposed study, suggests distances of up to 14 meter gains may be possible. Taking into account these data and based on our study team’s considerable clinical expertise, we decided that the minimal clinically important difference of 14 meters would be reasonable. Using the sample size calculation formula for ANCOVA in RCTs (α=.05; β=.1; rho=.72) [82], each group would require 21 participants. Borm et al [83] demonstrate that when rho lies between .2 and .8, ANCOVA further reduces the required sample size by 10-40% over change score. Accounting for an additional 4 degrees of freedom (one stratification factor for site at randomization and possibly three at analysis), an extra four participants per group (n=25) are required. Accounting for a conservative total group dropout rate of 25% and supported by physical activity clinical trials (8-24%) [84,85], 64 participants are required. Because the supervised sessions are conducted in groups of three, the sample size needs to be divisible by three. Therefore, a final n=72 will allow us to enroll a balanced n of 18 Wii.n.Walk and 18 controls at each site.

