#### Primary Outcome Measure

The Two-Minute Walk Test (2MWT) will be used to measure walking capacity as the primary outcome measure. Starting from a standing position, participants will be asked to walk as far as they can in a safe manner for 2 minutes over an indoor, flat, out-and-back course. The distance travelled to the nearest meter is recorded. The Canadian Physical Medicine and Rehabilitation Association’s Amputee Special Interest Group [40], and others [41,42], have recommended the 2MWT as the preferred measure of walking capacity. It is used in more trials of individuals with LLA [43-53] than any other measure, enabling us to compare our results with previous studies. The 2MWT has been validated with a number of LLA samples [41,42,51-53]. The 2MWT has demonstrated intra-rater reliability (intraclass correlation coefficient/ICC=.96), inter-rater reliability (ICC=.98) [51], and validity and responsiveness to change (mean 13.6, SD 19.9 meters) in individuals with LLA [52].

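### The 21 per group matches the ANCOVA formula only with the quoted SD of 19.9 m, which is described as an SD of change; if that SD was entered, the baseline correlation is counted twice and 72 participants give about 78% power, not 90%

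*Protocol article*

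**What the plan says.** All of this is in the protocol article.

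- **Sample Size Calculation, target:** "we decided that the minimal clinically important difference of 14 meters would be reasonable".
- **Sample Size Calculation, result:** "Using the sample size calculation formula for ANCOVA in RCTs (α=.05; β=.1; rho=.72) [82], each group would require 21 participants". The SD entered is not named.
- **Sample Size Calculation, SDs quoted:** there are four. One comes from patients being discharged from rehabilitation, where responsiveness "had a mean of 13.6 (SD 19.9) meters [52". One comes from a trial in younger amputees, where "the mean difference between treatment and control groups was 11.2 (SD 18.4) meters". Two are SDs of walking gains in the team's own work: 18.1 m (pilot) and 9.3 m (feasibility study).
- **Primary Outcome Measure:** the 13.6/19.9 pair appears again as "responsiveness to change (mean 13.6, SD 19.9 meters) in individuals with LLA".
- **Sample Size Calculation, next sentence:** for rho between .2 and .8, "ANCOVA further reduces the required sample size by 10-40% over change score".
- **Later steps:** 4 are added per group (25), 25% is allowed for dropout (64 in total), and the number is raised to 72, or 36 per group.
- **Primary Analysis:** the post-treatment score is compared by ANCOVA with baseline as a covariate.

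**The concern.** In an ANCOVA of the post-treatment score, the residual variance is the post-score variance times (1−ρ²). That factor belongs with a cross-sectional SD of the 2MWT, and the article gives none. All it offers are SDs of change or gain and one SD attached to a between-group difference. A change SD is already reduced by the correlation, so multiplying its square by (1−ρ²) takes credit for rho twice.

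At stake is the stated 90% power on the primary outcome. If 19.9 m is a change SD, the calculation rests on a residual SD of 13.8 m where its own inputs point to about 18.5 m. A non-significant result could then be read as stronger evidence against a 14 m effect than the trial can supply.

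**Working it through.** **Inputs.** δ = 14 m, α = .05 (sidedness not stated; two-sided reproduces the figure), β = .1, ρ = .72, and the four quoted SDs. 2(1.960 + 1.282)² = 21.015.

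**1. Reproduce the 21.** n = 21.015 × SD² × (1 − ρ²)/δ², with 1 − .72² = 0.4816.

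| SD (m) | n before rounding | n per group |
|---|---|---|
| 19.9 | 20.45 | 21 |
| 18.4 | 17.48 | 18 |
| 18.1 | 16.92 | 17 |
| 9.3 | 4.47 | 5 |

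Any SD from 19.68 to 20.17 m returns 21; of those quoted, only 19.9 lies in that range. One-sided α with 19.9 gives 17.

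**2. Test against the paragraph's own saving.** With no correlation factor, 21.015 × 19.9²/196 = 42.46, so 43. Since 19.9 is a change SD, 43 is the change-score sample size. The cut from 43 to 21 is 1 − 21/43 = 51%. The paragraph's 10-40% is 1 − (1+ρ)/2, which is 40% at ρ = .2 and 10% at ρ = .8. At ρ = .72 the saving is 14%.

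**3. Correct factor for a change SD.** Assume equal SDs at baseline and follow-up (not stated in the article). Then SD²change = 2σ²(1−ρ), and the ANCOVA residual variance is σ²(1−ρ²) = SD²change × (1+ρ)/2.

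- Factor: (1 + .72)/2 = 0.86.
- n = 42.46 × 0.86 = 36.52, so 37 per group.
- Implied post-score SD: 19.9/√0.56 = 26.6 m.
- Residual SD: 19.9 × √0.86 = 18.45 m, against 19.9 × √0.4816 = 13.81 m as planned.

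**4. The plan's later steps.** The plan goes from 25 to 32 per group by multiplying: 25 × 1.25 = 31.25. Applied to 37 + 4 = 41, this is 51.25, so 52 per group or 104 in total, against 72.

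**5. Power that 72 delivers for 14 m.** Noncentral t, residual SD 18.45 m, six model parameters (intercept, group, site, baseline, amputation level, age), no clustering allowance:

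| Dropout | Per arm | Power |
|---|---|---|
| 25% (planned) | 27 | 78% |
| 8% (low end of the cited range) | 33 | 86% |
| none | 36 | 89% |

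At 27 per arm, 90% power is reached only for a difference of about 16.6 m.

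**6. Sensitivity at 27 per arm.**

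- Follow-up SD 0.9 to 1.2 times baseline SD: requirement 33 to 42 per group, power about 83% down to 73%.
- Change SD of 18.4 or 18.1 m: requirement 32 or 31 per group, power 84% or 85%.
- Change SD of 9.3 m: requirement 8 per group, power over 99%.
- Triplet ICC of 0.10 (an assumed value; the article gives none): VIF = 1 + 0.10 × 2 = 1.2, power about 70%.

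**The case against.** The strongest objection is that the SD entered is inferred. A separately sourced or rounded post-score SD of 20 m also gives 21 (20.65) with no double counting, and the section says clinical expertise was used alongside the data. An SD of 18.4 m with the factor 2(1−ρ) gives 20.33, also 21, although that is not the ANCOVA formula the text names. This stands: a reader might infer that the error is proven, and the document does not prove it. What it does show is that the SD is unstated, and that the only quoted SD matching the result is described as one of change.

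Second, the conversion to 37 needs equal SDs over time. It also applies a rho of unstated source to an SD from patients at discharge, whereas the trial enrols community-dwelling prosthesis users. This stands too, and is why 37 comes with a range.

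Third, the plan calls 25% dropout conservative, and the feasibility SD of 9.3 m, from a sample like the trial's, would leave ample power. Both are fair, but 9.3 m is not an SD that yields 21, and even with no dropout the 19.9 m change SD gives 89%.

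A reader might also infer that the plan's own steps lead to 110 participants. They do not: 110 comes from dividing 41 by 0.75 (55 per group), while the plan multiplies by 1.25, which gives 104. Nor does the article support quoting 70% power as a finding, because the ICC behind it is an assumption.

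**Conclusion.** The point holds in conditional form. As written, the paragraph does not fit together: its 21 matches only an SD that the article calls one of change, and the implied 51% saving contradicts the 10-40% in its next sentence. If the change SD was entered, the requirement before allowances is about 37 per group rather than 21. At the planned dropout, power for 14 m is then about 78%, some 12 points below the stated 90%. Rounding up to 72 softens the shortfall and nearly removes it if nobody drops out.

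The size rests on three things: 19.9 m being the SD entered, equal SDs at baseline and follow-up, and rho = .72 applying to this population. Across SD ratios of 0.9 to 1.2, power at the planned dropout stays between about 73% and 83%. If a true post-score SD near 19.9 m was used, the 21 stands and only the missing citation needs repair.

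**What to change.** Keep N = 72 and rewrite the sample size paragraph.

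1. State the SD entered, its source, and whether it is an SD of change or of the post-treatment score.
2. If it is the 19.9 m change SD, apply (1+ρ)/2 to the change-score n, or convert to a post-score SD of 26.6 m before applying (1−ρ²). Replace 21 with about 37.
3. State the power that 72 participants give for 14 m (about 78% at 25% dropout, 86% at 8%, 89% with none), or the difference detectable with 90% power (about 16.6 m at 27 per arm).
4. If a genuine post-score SD near 19.9 m was used, cite it and leave the 21.
5. Label the equal-SD assumption, and any ICC used for the triplets, as assumptions.

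The cost is rewording and, if step 2 applies, a less favourable stated power. The fix needs no extra participants and no change to the design or analysis.

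### The 64 participants said to be required do not yield the plan's own 50 completers at 25% dropout (68 would), and the sample size makes no allowance for the VIF used in the analysis; the enrolled 72 covers the first gap and part of the second.

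*Protocol article*

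**What the plan says.** The Sample Size Calculation builds the target in steps. It sets the effect ("we decided that the minimal clinically important difference of 14 meters would be reasonable") and then gives the first result: "Using the sample size calculation formula for ANCOVA in RCTs (α=.05; β=.1; rho=.72) [82], each group would require 21 participants". Four per group are added for degrees of freedom, making 25. The dropout step follows: "Accounting for a conservative total group dropout rate of 25% and supported by physical activity clinical trials (8-24%) [84,85], 64 participants are required". The last step, from 64 to 72, is justified by the need for groups of three and by balance between arms and sites (18 per arm at each site). No ICC, VIF or design effect enters at any step.

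The Primary Analysis does provide for correlation within training groups. It defines VIF = 1 + ICC(M−1) and fixes M: "The M variable refers to the cluster size, which equals 3 in this study". The ANCOVA F "statistics will be divided by the VIF". The Secondary/Tertiary Analyses section applies the same adjustment.

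**The concern.** Two things do not fit. First, the dropout step appears to add 25% to the number needed, rather than divide by the 75% expected to remain. The number printed as required then misses the plan's own completer target. Second, the analysis carries a clustering penalty that the sample size ignores. A test statistic shrunk by the VIF has less power than the same statistic unshrunk, so β = .1 describes a test that the trial will not use unless the ICC is zero. At stake are a wrong figure for the required number and a power statement with an unstated condition.

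**Working it through.** **Inputs.** From the Sample Size Calculation: difference 14 m; "α=.05; β=.1; rho=.72"; 25 per group after the degrees-of-freedom allowance; dropout 25%; enrolment 72. From the Primary Analysis: M = 3. The section does not say which SD it used or whether the test is two-sided. The study that "had a mean of 13.6 (SD 19.9) meters" supplies an SD that, with a two-sided test, reproduces the plan's result. The ICC values below are assumptions.

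**Reproducing 21 per group.**
- Residual variance factor: 1 − 0.72² = 0.4816
- Residual SD: 19.9 × √0.4816 = 13.8 m
- n = 2 × [(1.960 + 1.282) × 19.9/14]² × 0.4816 = 20.4, rounded up to 21
- A one-sided test gives 17. The other SDs cited in the section (18.4, 18.1, 9.3) give 18, 17 and 5 two-sided.
- Adding 4 gives 25 per group, 50 in total.

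**Dropout step.**
- 25 × 1.25 = 31.25, rounded up to 32 per arm: 64, the stated figure
- 25/0.75 = 33.3, rounded up to 34 per arm: 68 (rounding the total instead, 50/0.75 gives 67, which cannot be split 1:1)
- Dividing by 1 − d gives 64 only for d of about 20–21%. Even at 24%, the top of the cited range, it gives 66.
- Completers from 64: 64 × 0.75 = 48, against 50 needed
- Completers from 72: 72 × 0.75 = 54, or 27 per arm

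Balanced triplets over two arms and two sites require a multiple of 12 (3 × 2 × 2). Rounding 68 up to such a multiple gives 72, the same as rounding 64 up.

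**VIF step.** With M = 3, VIF = 1 + 2·ICC. Dividing F by the VIF acts on power as if the residual SD were multiplied by √VIF. Two calculations follow, each with 14 m, residual SD 13.8 m and two-sided α = .05:
- A: noncentral t, 27 completers per arm, 2 × 27 − 2 − 4 = 48 degrees of freedom.
- B: normal approximation with the plan's four per group set aside, so 27 − 4 = 23 per arm.

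| Assumed ICC | VIF | Power A | Power B |
|---|---|---|---|
| 0 | 1.0 | 95% | 93% |
| .05 | 1.1 | 94% | 91% |
| .10 | 1.2 | 91.5% | 88% |
| .20 | 1.4 | 87% | 83% |

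Power reaches 90% at an ICC of about .13 under A, and between .05 and .10 under B.

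**The case against.** The strongest reply is that 64 is an intermediate line. The trial enrols 72, its 54 completers exceed 50, and a corrected 68 rounds to the same 72. That stands, so the dropout slip changes a printed figure and not the trial. The multiplication by 1.25 is also inferred, since the article does not write it out. But 48 completers against 50 does not depend on how 64 was reached.

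A reader might infer that 64 would leave the trial clearly underpowered. The numbers do not support this: with independent observations, 64 enrolled (24 completers per arm) gives about 93% by method A and 89% by method B (24 − 4 = 20 per arm). What 64 fails is the plan's own head count. Nor do the documents make 64 a fallback or stopping number.

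A reader might also infer that 72 tolerates an ICC of at most .04, because 27/25 = 1.08 = 1 + 2 × .04. That is the limit for keeping 25 effective participants per arm. It is not where 90% power is lost, because 25 per arm already includes the four added for degrees of freedom.

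On clustering, it can fairly be said that the correlation may be negligible and that the protocol speaks only of its possible presence. That also stands: the size of the gap is unknown. The omission is not in doubt, because the section lists every step to 72 and gives only divisibility and balance as the reason for the last one.

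**Conclusion.** The point holds in two limited parts. The required number is misstated: 64 should be 68 at 1:1 allocation, and the enrolled 72 already covers the difference. The power statement rests on independence, while the primary test is penalised for dependence. Under assumed ICCs from 0 to .20, 72 enrolled gives about 95% down to 87% power, or 93% down to 83% if the four per group are set aside. The stated 90% therefore survives small correlations and fails at moderate ones. These figures rest on an SD of 19.9 m, inferred because it reproduces 21 per group, on a two-sided test, on exactly 25% dropout spread evenly over the arms, and on ICC values that the documents do not supply. They do not show that the trial is too small.

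**What to change.** In the Sample Size Calculation, replace 64 with 68 and show the step as 25/(1 − 0.25) = 33.3, rounded up to 34 per arm. Keep N = 72. Add a sentence that states an assumed ICC with a range (0 to .20, for example) and the resulting VIF. Then report either the power that 72 delivers over that range after 25% dropout or the largest ICC at which it keeps 90%. Say which SD was used and how the four per group were treated, because the tolerated ICC depends on both.

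The cost is a few lines of text and a slightly less favourable power figure. No patients are added and the analysis does not change.
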